### Exclusion criteria

Participants with the following characteristics will be excluded: [14]

Pregnant individuals

Individuals with arrhythmia

Individuals with Thrombocytopenia

Individuals with Sickle Cell Anemia

Individuals with a pacemaker

Individuals with alterations in coagulation factors

History of cancer

History of hyperthyroid

### Discontinuation or interruption criteria

Participants reporting any discomfort during the procedures or showing sensitivity to laser application will be excluded from the analysis, and the procedures will be immediately discontinued upon reporting.

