### Sample

Individuals between 7 and 19 years of age with orofacial pain post-covid-19 will be invited to participate in the study. A convenience sample was chosen, totaling 180. Given the lack of definitive studies for sample size calculation regarding persistent COVID-19 symptoms, a convenience sample was used. Participants were chosen based on reported symptoms and inclusion criteria at the university outpatient clinic. This approach was necessary due to the evolving nature of post-COVID-19 symptomatology, which currently prevents standardized sample size determination.

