### Study variables

Sociodemographic information such as age, skin phototype [classified by the Fitzpatrick scale], weight and height. The primary outcome is orofacial pain, and the secondary outcomes are oxygen saturation, blood pressure, heart rate, local temperature, blood lactate levels, and hemoglobin levels. In addition to demographic, anthropometric, and hemodynamic variables, the penetrated energy will be quantified using a power meter, and information from orofacial pain and headache symptom questionnaires will be analyzed.

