### Randomization

The participants will be informed that they will be randomly assigned to one of the four study groups that will be compared. To allocate the participants to the groups, a stratification process will be carried out based on the answers to the questionnaires and the presence of orofacial pain symptoms and the presence of headache symptoms will be considered strata. Stratification will be carried out to balance the allocation of participants in each group according to stratum.

After stratification, participants will be randomized in a 1:1:1:1 ratio into the 4 groups. The randomization list will be generated by an independent researcher in random blocks of four, electronically via the ramdomizer.org website and kept in opaque envelopes. The allocation will only be revealed to the operating researcher at the time of the intervention. A study team member, separate from the researcher who will administer the intervention, will follow the random allocation sequence to assign participants to a study group and prepare study equipment and materials. Eligible participants will be randomly assigned to Group 1—Local Photobiomodulation, Group 2—Vascular Photobiomodulation, Group 3—Placebo Local Photobiomodulation, or Group 4—Placebo Vascular Photobiomodulation using stratified block randomization generated by the study statistician.

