### Patient and public involvement

Eligible individuals will receive comprehensive explanations about the study’s aims and procedures. They will provide consent, which will be both written and verbally confirmed. Patients will not participate in recruitment or trial implementation. After data analysis, volunteers may attend a meeting to receive the results. Any potential difficulties arising from the interventions will be evaluated by the patients. The confidentiality of all individuals will be safeguarded throughout the research process. Participants will be allowed to withdraw from the study at any time.

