## Discussion

The present study addresses a significant gap in the understanding of optimal dosimetry for photobiomodulation therapy in patients experiencing orofacial pain and tension headache post-Covid-19. The introduction of low-level laser therapy [LLLT] as a potential alternative for pain management underscores the importance of determining precise dosimetric parameters tailored to individual patient characteristics. This study’s objective to validate a dosimetry model based on anthropometric and hemodynamic variables is crucial for optimizing treatment efficacy and minimizing potential adverse effects associated with pharmacological interventions [9, 10].

An essential aspect of this research lies in its methodological approach, which involves a randomized assignment of participants to different treatment groups, including placebo controls. Such a design ensures rigorous evaluation of the effects of both local and systemic photobiomodulation therapies, thereby enhancing the reliability and validity of the findings. Furthermore, the comprehensive data collection process, encompassing demographic, anthropometric, and hemodynamic variables, as well as measurements of skin and tissue characteristics, enables a thorough investigation of the factors influencing treatment outcomes.

The study’s incorporation of Monte Carlo simulation represents a novel and sophisticated analytical technique for elucidating the relationship between light penetration profiles and key variables, such as BMI and tissue layer thicknesses. By systematically exploring these associations, the research aims to develop a personalized dosimetry model, thereby advancing the precision and effectiveness of photobiomodulation therapy.

The discussion also highlights the potential implications of the study findings for clinical practice, particularly in the context of managing orofacial pain in post-Covid-19 patients. Given the growing recognition of the long-term effects of Covid-19 on various physiological systems, including pain perception and modulation, the validation of a dosimetry model tailored to this population is of paramount importance.

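### Removing participants with discomfort or laser sensitivity from the analysis after randomisation leaves the active-versus-placebo comparison of pain open to bias

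*Protocol article*

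**What the plan says.** One sentence under Discontinuation or interruption criteria does two things. It defines who leaves the analysis: "Participants reporting any discomfort during the procedures or showing sensitivity to laser application will be excluded from the analysis". It also sets a consequence for treatment: "the procedures will be immediately discontinued upon reporting". Only the first part is at issue here.

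Under Randomization, "participants will be randomized in a 1:1:1:1 ratio into the 4 groups", and "The allocation will only be revealed to the operating researcher at the time of the intervention". Under Sample, "A convenience sample was chosen, totaling 180". Under Study variables, "The primary outcome is orofacial pain, and the secondary outcomes are oxygen saturation, blood pressure, heart rate, local temperature, blood lactate levels, and hemoglobin levels". The Interventions section says that Groups 3 and 4 follow the procedures of Groups 1 and 2, with a device that gives the sound signal but no laser light.

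Nothing in the article returns the excluded participants to a main or a sensitivity analysis.

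**The concern.** Randomisation protects a comparison only as long as the groups analysed are the groups randomised. Here removal depends on something that happens after allocation and that the allocated treatment can influence. If more participants leave one arm than its comparator, and those who leave have worse (or better) pain than those who stay, the remaining groups differ even when the treatment does nothing.

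At stake is the comparison on the declared primary outcome. The Discussion relies on the randomised, placebo-controlled design: "Such a design ensures rigorous evaluation of the effects of both local and systemic photobiomodulation therapies". Pain outcomes that are not collected after a participant stops cannot be recovered later.

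**Working it through.** **Does the rule act after randomisation and can it depend on arm?**

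- Timing. The operator learns the allocation when the intervention takes place. A reaction to the laser application comes after that, so removal for it is post-randomisation.
- Sensitivity to the laser. The placebo devices emit no light, so a true reaction to light can occur only in Groups 1 and 2.
- Discomfort. This can occur in all four groups. The Data collection section describes a finger puncture and a power-meter sensor placed inside the cheek, and the placebo groups undergo the same procedures as the active ones.
- Link to outcome. The primary outcome is orofacial pain. That discomfort during application goes with worse pain is plausible, but the article does not establish it.

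The conditions for bias can therefore be met, but the article does not show that they will be.

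**How large could it be?** There is no figure in the article to reproduce: it states no alpha, power, effect size, SD or discomfort rate. The only input from the article is 180 / 4 = 45 per arm. The rest is assumed:

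- no true effect, and pain in SD units with SD 1;
- a fraction f_A excluded from an active arm and f_P from its placebo;
- excluded participants d SD worse than those retained in the same arm;
- two-sided test at 5%, normal approximation.

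If an arm's overall mean is 0 and a fraction f who are d SD worse are removed, the retained mean shifts by f × d in the favourable direction. Hence:

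- Bias = (f_A − f_P) × d
- SE = √[1/(45(1 − f_A)) + 1/(45(1 − f_P))]
- Type I error = P(Z > 1.96 − bias/SE) + P(Z < −1.96 − bias/SE)

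| Excluded, active v placebo | d (SD) | Left, active v placebo | Bias (SD) | SE | Bias/SE | Type I error |
|---|---|---|---|---|---|---|
| 2% v 0% | 1.0 | 44.1 v 45 | 0.02 | 0.212 | 0.09 | 5.1% |
| 10% v 3% | 0.5 | 40.5 v 43.65 | 0.035 | 0.218 | 0.16 | 5.3% |
| 10% v 3% | 1.0 | 40.5 v 43.65 | 0.07 | 0.218 | 0.32 | 6.2% |
| 10% v 0% | 1.0 | 40.5 v 45 | 0.10 | 0.217 | 0.46 | 7.5% |
| 20% v 0% | 1.0 | 36 v 45 | 0.20 | 0.224 | 0.89 | about 14.5% |

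Last row written out: bias = 0.20 × 1 = 0.20; SE = √(1/36 + 1/45) = 0.224; ratio = 0.894; type I error = P(Z > 1.066) + P(Z < −2.854) = 0.143 + 0.002, about 14.5%. The SE must use the participants left after exclusion. Keeping 45 in both arms gives SE = √(2/45) = 0.211 and 15.8%, which is too high.

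Equal exclusion fractions with the same d give zero bias. Reversing the fractions (3% active v 10% placebo, d = 1) gives −0.07 SD, against the active device, with the same 6.2%. If all randomised participants are analysed with their outcomes, the bias from this rule is zero.

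**The case against.** The strongest objection is that direction and size are unknown. Discomfort can be reported in a placebo arm. If active treatment relieves pain, discomfort might even be commoner under placebo, and the bias would then run against the device. In Groups 2 and 4 the device is applied over the radial artery, away from the painful region, so the link between discomfort and orofacial pain is weaker there. The introduction describes low-level laser therapy as non-invasive and safe, so 20% v 0% is an extreme case, and at 2% the effect is negligible. All of this stands. A reader might infer from the rule that the comparison is biased and that the bias flatters the device. The article supports only that it is open to bias, with that direction the more likely one.

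A reader might also infer that the trial could not report how often it caused discomfort. The article does not say that. Removing participants from the analysis does not forbid counting them by arm, and applying the rule requires that they be identified. Under Patient and public involvement it adds: "Any potential difficulties arising from the interventions will be evaluated by the patients". What holds is narrower: Study variables lists no tolerability outcome, so nothing shown requires reporting by arm.

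Third, the main stated aim is to validate a dosimetry model by comparing measured with simulated light transmittance, which this rule barely touches. That is fair, but pain is the declared primary outcome, and the Expected results section looks to a comparison of vascular and local treatment on it.

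Finally, an analysis plan that is not shown may define the analysis sets. That would answer a gap, but this is an explicit rule. A plan that retained these participants would contradict it.

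**Conclusion.** The point holds as a risk of bias. The exclusion is fixed in current text, follows allocation, has one trigger that can truly occur only in the light-emitting arms, and may be related to the primary outcome. Its size cannot be read from the article. On the assumptions above (no true effect, 45 randomised per arm, excluded participants 0.5 to 1 SD worse), type I error ranges from barely above nominal, about 5.1% at 2% v 0% excluded, to about 14.5% at 20% v 0%. These figures are illustrations, not estimates for this trial. Correction is still warranted because the rule bears on the primary randomised comparison and the repair is cheap.

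**What to change.** Separate the two parts of the sentence.

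- Leave the interruption of procedures as it is; no change to that rule is proposed.
- Delete the clause that removes these participants from the analysis, and state that all randomised participants are analysed in their allocated group.
- State that remaining outcomes are collected after interruption wherever the participant agrees.
- Report discomfort and laser sensitivity by arm.
- If a set without these participants is wanted, use it only as a sensitivity analysis.

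The cost is an amended sentence and minor extra follow-up of those who stop.

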### Interventions

#### Group 1 –Local photobiomodulation

The treatment will be administered over 2 weeks, totaling 4 sessions [2 sessions per week] with an average duration of 6 minutes per session.

Participants will be positioned in a clinical chair for the application of photobiomodulation. The interventions will be conducted by a trained professional. Group 1 will receive photobiomodulation using the Therapy EC–DMC device, with a red wavelength of 660 nm and power of 100 mW, properly calibrated, delivering 6J per point [60 seconds] at 2 points in the masseter muscle region, 1 point in the left temporal muscle,1 point in the right temporal muscle, 1 point in the left trapezius muscle in the cervical region, 1 point in the right trapezius muscle. The total application time will be 4 minutes per session.

At the time of application, only the participant receiving the treatment, the researcher responsible for the treatment, and the guardian will be present. Everyone will wear specific goggles for eye protection. The equipment’s tip will be disinfected with 70% alcohol and covered with disposable transparent plastic [PVC] to prevent cross-contamination, while the facial area to be irradiated will be cleaned with a 0.2% Chlorhexidine solution. During the applications, the participant will remain seated, with the Frankfurt plane parallel to the ground. Energy penetration will be analyzed at one of the points on the masseter muscle.

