#### Group 2 –Vascular photobiomodulation

Vascular Photobiomodulation [VBMP] will be applied using the same device, with an infra-red wavelength of 808 nm and 100 mW, directing the light beam to the radial artery region for 10 minutes per session.

The participant will be seated in a comfortable chair with lateral support for resting their arms during the application. At the time of application, only the participant receiving the treatment, the researcher responsible for the treatment, and the guardian will be present. Everyone will wear specific goggles for eye protection. The active part of the bracelet will be covered with disposable transparent plastic [PVC] to prevent cross-contamination, and for hygiene reasons, the area to be irradiated will be pre-cleaned with a 0.2% Chlorhexidine solution. During the applications, the participant will remain seated, with the Frankfurt plane parallel to the ground. A new treatment method will be administered for 2 weeks, totaling 4 sessions [2 sessions per week] with an average duration of 10 minutes per session.

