#### Group 3 –Placebo local photobiomodulation

Group 3 will undergo the same procedures described for Group 1, but the equipment will emit only the sound signal, exactly like the equipment used in Group 1, without the emission of laser light.

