#### Monte Carlo simulation

The Monte Carlo technique will be employed to simulate the fluence profile, energy deposited in different tissue layers of the cheek and index finger, and transmittance, using light of wavelengths 660 nm and 808 nm. In an initial phase, a Monte Carlo model will be developed, considering the morphological structure of the tissues to be treated, approximating their structure to a planar and laminar model consisting of four layers: epidermis, dermis, subcutaneous fat, and muscle [15].

The thicknesses of each layer will be obtained from the literature, and their values will be varied in predefined intervals consistent with literature findings for different age groups and BMI values. The optical properties of each layer, including absorption and scattering coefficients, anisotropy coefficient, and refractive index, will be gathered from bibliographic research, considering the expected variability for the sample under study.

A model for the absorption coefficient will be used, accounting for blood content in each layer, blood oxygen saturation level, as well as fractions of fat, melanin, and water in each tissue layer. Based on the preliminary study, a database will be established aiming to establish a relationship between energy deposited in tissues and different anthropometric characteristics [13, 16].

Special attention will be given to the relationship between energy deposited in the epidermis and muscle, to establish a compromise between safety limits and treatment effectiveness. Simulated transmittance values will be subsequently compared with values measured in volunteers, considering measurements of tissue thickness by ultrasound, skin type, BMI, and blood saturation levels. A computational implementation of the tissue optical model and the Monte Carlo simulation model will be developed based on Marti et al.’s MCMatlab code, available online [https://github.com/ankrh/MCmatlab], using Matlab® software, version 2022.

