### Expected results

It is expected that we will ascertain whether there is a difference between the effects of vascular and local photobiomodulation on orofacial pain, with the study’s aim to develop and validate a dosimetric model for individualized protocols based on the unique characteristics of each patient.

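### Dropping randomised participants who report discomfort or laser sensitivity from the analysis could bias the pain comparisons, by an unknown amount and in an unknown direction

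*Protocol article*

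**What the plan says.** The rule stands in the protocol article under Discontinuation or interruption criteria: "Participants reporting any discomfort during the procedures or showing sensitivity to laser application will be excluded from the analysis". It continues that "the procedures will be immediately discontinued upon reporting". It is separate from the eligibility exclusions, which have their own list under Exclusion criteria. Nothing elsewhere in the article returns these participants to any analysis.

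The related text is as follows.

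- Study variables: "The primary outcome is orofacial pain".
- Randomization: four arms in equal ratio, with the allocation disclosed to the treating researcher only when the intervention is given.
- Group 1: the active local arm has the laser tip on facial and neck muscle, "delivering 6J per point [60 seconds] at 2 points in the masseter muscle region", plus four further points on the temporal and trapezius muscles.
- Group 2: the active vascular arm is treated at the wrist, "directing the light beam to the radial artery region for 10 minutes per session".
- Groups 3 and 4: the sham arms follow the procedures of their active counterparts, but "without the emission of laser light".
- Expected results: the trial should show "whether there is a difference between the effects of vascular and local photobiomodulation on orofacial pain". The Discussion relies on random assignment with placebo controls for the rigour of the evaluation.

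**The concern.** The rule selects the analysed population by something that happens under the allocated treatment. Randomisation balances the arms as allocated. It does not balance what is left after people are removed for how they responded to their arm.

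Two features make this more than a formality here. Everyone enrolled has pain or headache, and the local arms are treated on the face and neck, so discomfort during treatment may well be correlated with the pain outcome. The triggers also need not occur equally often in each arm. If both hold, an arm can look better or worse simply because of who was removed. That would affect both the active-versus-sham and the local-versus-vascular comparisons of pain.

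A smaller loss comes on top. Those who react to the dose carry the most information on tolerability, and some of their light-transmission readings might be discarded as well.

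**Working it through.** The plan has no figure of its own to reproduce: 180 is a convenience sample, and no error rate, effect size or expected rate of discomfort is given.

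**Inputs from the protocol article**

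- Sample and Randomization: 180 / 4 = 45 per arm, so 2 × 45 = 90 participants receive light.
- Group 1 and Table 1: 6 points × 4 sessions = 24 contacts in a local arm.
- Group 2 and Table 1: 1 site × 4 sessions = 4 contacts in a vascular arm, at 10 minutes each.
- Local duration: 6 points × 60 s = 6 minutes per session, although the Group 1 text also gives a total of 4 minutes. On either figure it is shorter than the vascular session.

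**Step 1. Where can the triggers differ?**

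- Active against sham, same route: tip contact is the same. Only a true reaction to light is specific to the active arm, and a sham participant can still report sensitivity.
- Local against vascular: site, number of contacts and duration all differ.
- Shared steps (finger puncture, ultrasound, sensor inside the cheek): discomfort may be balanced. Any that arose before randomisation would not bias the comparison.

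**Step 2. Illustration with a relief proportion.** Assumed: no true difference, the same relief rate in two arms of 45, and 5 participants dropped from one arm and none from the other. If R of 45 have relief and r of the 5 dropped had relief, the proportion analysed is (R − r) / 40.

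| True relief in both arms | All 5 unrelieved | 5 like the rest | All 5 relieved |
|---|---|---|---|
| 40% (R = 18) | 18/40 = 45.0% (+5.0 points) | 16/40 = 40.0% (0) | 13/40 = 32.5% (−7.5 points) |
| 60% (R = 27) | 27/40 = 67.5% (+7.5 points) | 24/40 = 60.0% (0) | 22/40 = 55.0% (−5.0 points) |

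With one participant dropped (1/45 = 2.2%) at 40% relief, the range is 17/44 = 38.6% to 18/44 = 40.9%.

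**Step 3. Illustration with a pain score.** Assumed: no true difference, two-sided 5% test, normal approximation. A fraction e1 is excluded from one arm and e0 from the other, and the mean pain of those excluded is d SD above that of those retained.

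- Bias in SD units: b = −(e1 − e0) × d.
- Standard error: SE = √(1/n1 + 1/n0), with n1 = 45(1 − e1) and n0 = 45(1 − e0).
- Actual type I error: Φ(−1.96 − b/SE) + 1 − Φ(1.96 − b/SE).

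For e1 = 10%, e0 = 0 and d = 1: b = −0.10, SE = √(1/40.5 + 1/45) = 0.217 and b/SE = −0.46. The type I error is 0.067 + 0.008 = 0.075.

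| e1 | e0 | Size of bias, d = 0.5 to 1.0 | Type I error |
|---|---|---|---|
| 2% | 0 | 0.01 to 0.02 SD | 0.050 to 0.051 |
| 5% | 0 | 0.025 to 0.05 SD | 0.052 to 0.056 |
| 10% | 5% | 0.025 to 0.05 SD | 0.052 to 0.056 |
| 10% | 0 | 0.05 to 0.10 SD | 0.056 to 0.075 |
| 15% | 0 | 0.075 to 0.15 SD | 0.063 to 0.105 |

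If those excluded have less pain than the rest, the bias changes sign and the type I error is the same. If e1 = e0 with the same d, the bias is zero and only precision is lost.

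**The case against.** The best defence is that the rule may rarely bite. The Introduction describes the therapy as non-invasive and safe. At about 2% exclusion the effect is negligible, and it becomes material only at roughly 10% to 15% in one arm with none in the other. Sham follows the same procedures as its active counterpart, so contact discomfort should be similar within a route. This bears on the size of the problem and stands. It does not defend the rule: if events are rare, keeping these participants costs almost nothing. Nor is this a detail left to an analysis plan, because the article itself fixes who is removed.

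A reader might infer more than the documents support.

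- **That the triggers are known to be unequal across arms.** No rates are given. Only a true reaction to light is specific to the active arms by design. The rest is inference.
- **That discomfort is the primary outcome under another name.** Discomfort during a procedure is not the pain assessment, and discomfort at the wrist or finger is not orofacial pain. Correlation is plausible but not shown.
- **That the rule favours active treatment.** The direction is unknown, and Step 2 shows losses as well as gains.
- **That the model's safety limits would be set without the sensitive participants.** The Monte Carlo simulation section does seek "to establish a compromise between safety limits and treatment effectiveness", but from simulated energy in the epidermis and muscle. Nothing there says that reported sensitivity feeds those limits.
- **That observation ends on a report.** The text says that procedures stop. How far this reaches is detail that a condensed article may leave out, and it is not counted as a fault.

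**Conclusion.** The point holds in limited form. The protocol article fixes an exclusion after randomisation whose triggers may be related to both the outcome and the arm. The resulting pain comparisons would no longer be fully protected by randomisation. That the rule is stated is certain; the imbalance it causes, its direction and its size are not.

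Under the assumptions shown, the shift runs from none, or almost none at about 2% exclusion, to between −7.5 and +7.5 percentage points when 5 of 45 are dropped from one arm. On a pain score, 10% to 15% one-sided exclusion gives a bias of 0.05 to 0.15 SD and a type I error of 0.056 to 0.105. These figures rest on assumed rates and describe no expected result. The loss of tolerability information, and possibly of transmittance readings, is a secondary cost. Stopping irradiation at once is sound and is not in question; only the removal from the analysis should change.

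**What to change.** Reword the Discontinuation or interruption criteria along these lines:

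- Irradiation stops at once when a participant reports discomfort or shows sensitivity.
- With the participant's agreement, the pain and headache questionnaires and the non-invasive measurements continue at the planned dates.
- All randomised participants are analysed in the group to which they were allocated.
- Discomfort and sensitivity are reported by arm.
- Light-transmission readings completed before the stop stay in the comparison of measured with simulated values.
- An analysis without these participants may be shown as a sensitivity analysis only.

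Analysing everyone as allocated removes the selection that this rule creates. The cost is some visits for assessment only and some missing values from those who decline, which the analysis must handle. Under Ethical considerations and dissemination, the change must also be notified to the ethics committee and entered in the registry. No new visit or measurement is needed.
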